### Concealment mechanism {16b}

The random sequence will be immediately sent to a designated nurse who prepare the fluids and medications. For the tirofiban group, a 50-mL volume of tirofiban fluid and a 5-mL volume of 0.9% sodium chloride (labeled as heparin) will be prepared. For the heparin group, a heparin fluid and a 50-mL 0.9% sodium chloride (labeled as tirofiban) will be prepared.

### Implementation {16c}

Doctors and nurses working near the bed will have no idea which fluid is genuine medication. These fluids will be infused according their label names. Thus, all subjects, site staff, sponsor staff, assessors, and data analysts will be blinded to randomization outcomes.

## Assignment of interventions: blinding

### Who will be blinded {17a}

All subjects, site staff, sponsor staff, staff (with exceptions as indicated below), assessors, and data analysts will be blinded to randomization outcomes until the database is unlocked. Exceptions will include (1) nurses who prepare the fluids and medications (heparin, tirofiban, or just 0.9% sodium chloride), (2) computer programmers involved in randomization and drug management processes, and (3) the biostatistician creating reports for the Data and Safety Monitoring Board (DSMB).

### Procedure for unblinding if needed {17b}

The DSMB will periodically examine all safety and outcomes data. Appropriate information regarding adverse occurrences will be systematically gathered and presented to regulatory authorities.

Emergency unblinding will be performed only when necessary for subject safety. Only those individuals who are required to know treatment allocation will be given this information in such an event. If medically appropriate, all subjects will resume the study treatment after recovery and continue to do so until the end of the study.

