## Abstract

**Background:**

For complete revascularization, patients with diffuse coronary artery disease should have a coronary endarterectomy and a coronary artery bypass graft (CE-CABG). Sadly, CE can lead to a lack of endothelium, which raises the risk of thrombotic events. Even though daily dual antiplatelet therapies (DAPT) have been shown to reduce thrombotic events, the risk of perioperative thrombotic events is high during the high-risk period after CE-CABG, and there is no consistent protocol to bridge DAPT. This trial aims to compare safety and efficacy between tirofiban and heparin as DAPT bridging strategies after CE-CABG.

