## Introduction

### Background and rationale {6a}

Creation of distal surgical anastomoses can be difficult in patients with severe complex or diffuse coronary artery disease (CAD) undergoing coronary artery bypass grafting (CABG). Incomplete revascularization can affect patient survival and quality of life [1]. Coronary endarterectomy (CE) was first introduced in 1957 by Bailey et al. and is now being performed as an adjunct with CABG (CE-CABG) in patients with diffuse CAD to achieve complete revascularization [2]. Although long-term survival is comparable between CE-CABG and CABG alone, early surgical outcomes related to postoperative myocardial infarction (POMI) and mortality are worse in those undergoing CE-CABG [3–5]. These patients mainly experience graft occlusion owing to thrombosis in endarterectomized regions. During endarterectomy, the vascular intima is carefully dissected and removed, which exposes the subendothelial tissue to blood flow, causing fibrin platelet mural thrombus and activation of the coagulation cascade [6–8]. Dual antiplatelet therapy (DAPT) and postoperative anticoagulation may play a role in avoiding POMI after CE-CABG.

Current clinical guidelines recommend DAPT as soon as feasible after CABG and continuation for at least 12 months [9]. However, the use of antithrombotic medication within 24 h of CE-CABG is controversial. Reported rates of hemorrhage, POMI, and short-term mortality after CE-CABG vary substantially between studies [10–12]. Some centers have begun to use a heparin infusion 4 h after surgery in patients undergoing CE if the chest tube output is less than 50 to 100 mL/h. However, the incidence of POMI appears to be relatively high even with early heparin infusion [10, 11].

Tirofiban is a small-molecule peptide that selectively inhibits fibrinogen–platelet GP IIb/IIIa binding and reduces ischemic events in patients with acute coronary syndrome (ACS) undergoing percutaneous coronary intervention [13, 14]. Since perioperative use of GP IIb/IIIa inhibitors does not increase surgical bleeding after CABG [15–17], we hypothesized that early tirofiban administration before initiation of DAPT reduces the incidence of thrombosis and POMI after CE-CABG but does not increase bleeding incidence or severity.

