**Fig. 1 Fig1:**
[figure not shown]
Study design. TIA, transient cerebral ischemia; IABP, intra-aortic balloon pump; ECMO, extracorporeal membrane oxygenation

Two hours after randomization, heparin (100 IU/kg) will be administered intravenously in 5 mL of 0.9% sodium chloride every 4 h in the heparin group. In the tirofiban group, tirofiban (0.05 g/kg/min) will be infused over 22 h using a micropump starting within 30 min of randomization. To maintain treatment blinding, a 5-mL volume of 0.9% sodium chloride will be administered to patients in the tirofiban group, and patients in the heparin group will receive an infusion of 0.9% sodium chloride via micropump. Only the nurses who prepared the fluids will know which are genuine medications. Once heparin or tirofiban stop at 24 h, DAPT will be initiated the next day of surgery and continued daily (ticagrelor 90 mg twice daily plus aspirin 100 mg daily in patients with platelet count ≥ 9 × 10^9^ cells/L; aspirin alone daily in patients with platelet count < 9 × 10^9^ cells/L). For patients who are unable to be extubated within 24 h, heparin or tirofiban will be continued until the patient is extubated, at which point DAPT will start. The timeline of antithrombotic drugs is showed in Fig. 2.

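### The sentence on resuming treatment after emergency unblinding, if it means the allocated heparin or tirofiban, conflicts with the stop at 24 h or extubation

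*Protocol article*

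**What the plan says.** The unblinding section {17b} allows emergency unblinding only where a subject's safety requires it, and restricts who learns the result: "Only those individuals who are required to know treatment allocation will be given this information in such an event". The next sentence deals with what follows: "If medically appropriate, all subjects will resume the study treatment after recovery and continue to do so until the end of the study".

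The dosing text under Randomization and intervention (the paragraph after Fig. 1) sets a short course. Tirofiban "will be infused over 22 h using a micropump starting within 30 min of randomization". Heparin is given every 4 h, starting 2 h after randomization. Then: "Once heparin or tirofiban stop at 24 h, DAPT will be initiated the next day of surgery and continued daily". There is one extension, for patients not extubated within 24 h: "heparin or tirofiban will be continued until the patient is extubated, at which point DAPT will start".

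The stated purpose fits a short course. The abstract says that the trial aims to "compare safety and efficacy between tirofiban and heparin as DAPT bridging strategies after CE-CABG", and the hypothesis in Background and rationale {6a} is that "early tirofiban administration before initiation of DAPT reduces the incidence of thrombosis and POMI after CE-CABG".

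**The concern.** The two sections give different stops for what appears to be the same drug. The dosing text ends it at 24 h or at extubation. The unblinding section ends it with the study. A site that followed the unblinding sentence literally would restart an intravenous antithrombotic in a patient who had just had a safety emergency, and would find no instruction there to stop it when DAPT begins. The two could then overlap, which the dosing text is arranged to avoid. The question is one of patient safety and clear instructions. It does not touch the statistical design.

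**Working it through.** No figure in the plan is in dispute, so the check is mainly a comparison of texts, with simple arithmetic to show the scale.

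**1. What study treatment most naturally means.** The unblinding section does not define it. The evidence for the allocated drug is:
- The sentence just before it concerns treatment allocation. DAPT is given in both arms and is not allocated.
- The dosing text says that the saline dummies protect treatment blinding. Only the heparin and tirofiban preparations have dummies, and the blinding section {17a} names only heparin, tirofiban and saline as what the unblinded nurses prepare.
- Blood tests are timed at 4 and 10 h after treatment initiation, which means the start of heparin or tirofiban, not of DAPT.
- Both drugs are described as a bridge to DAPT, and tirofiban as given before DAPT starts.

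**2. Planned length of the allocated drug.** Inputs: randomization 2 h after surgery (Sequence generation {16a}); the tirofiban and heparin timings above; extubation by 24 h. The dosing text does not say from when its 24 h is counted, and the timeline figure is not shown. I assume from surgery, which agrees with the tirofiban timing.
- Tirofiban: starts at 2 to 2.5 h, runs 22 h, and ends at 2 + 22 = 24 h to 2.5 + 22 = 24.5 h after surgery.
- Heparin: starts at 2 + 2 = 4 h and stops at 24 h, so it covers 24 − 4 = 20 h. Doses every 4 h fall at 4, 8, 12, 16 and 20 h, which is 5 doses before the stop.

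If the 24 h were counted from randomization, the stop would fall at 2 + 24 = 26 h after surgery. The comparison below would hardly change.

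**3. Length under the unblinding sentence.** It depends on what the end of the study means, which the section does not say.
- If it is the 30-day endpoint (an assumption): 30 × 24 = 720 h, against a planned stop at 24 h, or 720 / 24 = 30 times as long.
- If it is the end of the whole trial, which Trial status expects in late 2026: longer for any patient whose day 30 falls before then.

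Neither matches a stop at 24 h or, in the ordinary case, at extubation. The conflict therefore does not depend on which end is meant. These hours compare two instructions. They do not measure harm.

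**4. Whether the qualifier resolves it.** The condition of medical appropriateness governs whether treatment is resumed. The duration is stated separately and is not tied to the dosing schedule.

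**The case against.** The strongest reply is that study treatment may mean the whole regimen. Explanation for the choice of comparators {6b} and the Discussion both describe tirofiban infusion followed by DAPT, and the dosing text has DAPT given daily with no end date. On that reading, resuming and carrying on is close to what the dosing text prescribes. This stands as a possible reading, and it reduces the fault to an undefined term. It does not make the sentence clear, since the study's end is not stated as a DAPT duration anywhere in the dosing text.

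A second reply is that the dosing section is the specific one, and that resuming may just mean returning to its schedule. That is sensible practice, but the unblinding sentence states its own duration and does not refer back.

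A third reply is that exposure is limited, and this is right. The text after Fig. 2 halves or stops the drugs on coagulation results and stops tirofiban for a low platelet count. Section {11b} has patients with a serious adverse event counselled to withdraw. Resumption needs medical judgement. These provisions reduce the risk, but none sets a course length.

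A reader might infer that the protocol orders an infusion until late 2026. The documents do not support this. The passages that point to the end of the whole trial concern safety reporting and recruitment status, not an individual's treatment, and Provisions for post-trial care {30} suggests a patient-level end near 30 days. No site would plausibly act on the extreme reading. A reader might also take the sentence to cover every trial subject. Its place under emergency unblinding makes unblinded subjects the fair reading.

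**Conclusion.** The point holds in a conditional form. If study treatment means the allocated heparin or tirofiban, which is the more natural reading, the unblinding section conflicts with the stop at 24 h or extubation, wherever the end of the study is placed. If it means infusion followed by DAPT, the term is only undefined. It would go too far to call this an outright contradiction on every reading, or a substantial hazard.

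The size is minor. Emergency unblinding is meant to be rare, so few patients should be affected. The documents give no unblinding rate, so the number cannot be estimated. Sample size, power, alpha and the analyses are unaffected. The correction is still worth making, because this is an operative dosing instruction that applies just after a safety emergency. My confidence is medium, because the conclusion rests on how an undefined term is read and the full protocol, which may define it, is not shown.

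**What to change.** In Procedure for unblinding if needed {17b}, replace the duration with wording such as: the allocated heparin or tirofiban may be resumed only if medically appropriate and only within the treatment window given under Randomization and intervention (to 24 h, or to extubation if later); thereafter DAPT follows as set out there, and the allocated drug is not restarted. If DAPT was meant, name it. It would also help to state from when the 24 h is counted.

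The cost is one sentence in a protocol amendment and a note to the sites. No patients, visits or procedures are added, and nothing in the statistics changes.

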## Data collection and management

### Plans for assessment and collection of outcomes {18a}

Data will be collected using a study-specific eCRF (Digital Health China Technologies Co., LTD, Beijing, China) and entered onto a paper case report form. Throughout the trial, data management personnel will validate the data. Data fields will be checked and any missing data or inconsistencies will be corrected before downloading into the study database. All identifying information will be hidden to protect patient confidentiality. All study personnel will have 24-h access to the study coordinating center. A data monitoring committee will monitor data accuracy and completeness, evaluate adverse events, and make the final decision to terminate the trial. When all data management and statistical data validation procedures have been completed, the database will be unlocked to perform the final analysis.

### Plans to promote participant retention and complete follow-up {18b}

There are no further plans for intervention engagement tactics beyond those that have already been described.

### Data management {19}

The DSMB will consist of a chair, co-chair, and members with recognized expertise in clinical trials, cardiovascular disease, and biostatistics who are not involved in the routine conduct of the THACE-CABG trial. The DSMB will be responsible for two main tasks. First, it will regularly assess the safety and effectiveness of the drugs under investigation by reviewing periodic updates provided during the course of the study. Second, it will provide recommendations to the trial’s chair and vice chair regarding the appropriate course of action, which may involve continuing, modifying, or terminating the study.

The DSMB’s primary responsibility is study oversight. Subject risks and benefits will be determined after an unblinded evaluation of aggregate data. The DSMB charter and meeting schedule will be finalized during the first meeting. A biostatistician, who will not be blinded for report preparation, will attend meetings to provide support. Conference attendees will be able to hear updates and ask questions of the trial’s chair and/or primary investigators during the open section of the conference.

### Confidentiality {27}

Only the lead investigator and necessary staff will have access to collected data. To protect patient confidentiality, each subject’s laboratory samples, completed forms, reports, and other data will be identified by a special participant ID number.

### Plans for collection, laboratory evaluation, and storage of biological specimens for genetic or molecular analysis in this trial/future use {33}

Not applicable: no biological specimens will be collected.

## Statistical methods

### Statistical methods for primary and secondary outcomes {20a}

Patient characteristics will be compared using the two-sample *t*-test or Wilcoxon rank sum test for continuous variables and the chi-square test or Fisher’s exact test for categorical variables. Variables that significantly differ between groups will be used as covariates for efficacy analysis.

Both intention-to-treat and per-protocol analyses will be conducted. The primary safety outcome will be compared between groups using a one-sided non-inferiority test. The primary efficacy outcome will be evaluated using the chi-square test or Fisher’s exact test.

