## Intervention description {11a}

### Standard procedure before randomization

Before surgery, patients hospitalized for isolated CABG will receive the following standard antithrombotic regimen: aspirin will be administered up to the day of the procedure; clopidogrel, ticagrelor, and prasugrel will be stopped at least 5, 5, and 7 days before, respectively.

CE-CABG will be performed by experienced surgeons via a median sternotomy utilizing either an on- or off-pump grafting technique. CE will be indicated for patients with: (1) a long, diffusely diseased coronary artery segment or severely calcified coronary artery, or (2) severe long-segment in-stent restenosis with or without major side branch occlusion [23]. CE is occasionally unanticipated prior to CABG surgery. CE-CABG is typically the last option for obtaining full revascularization. Patients who do not undergo CE have a better prognosis than those that do when antithrombotic medication is used according to current recommendations; therefore, they are not required to receive tirofiban therapy and will not be included.

Graft flow and PI will be assessed at the end of the operation before protamine administration using the VeriQ Flowmeter System (MediStim ASA, Horten, Norway), which is based on an ultrasonic transit time flow meter. If the PI is more than 5, the graft must be anastomosed again. If it remains above 5, the surgery is deemed a failure and the patient will be removed from the study.

After the procedure, protamine will be administered to reverse the heparin (100 IU heparin: 1 mg protamine) and the active coagulation time will be corrected to the pre-heparinization value of 5%. Chest tube blood loss will be evaluated 2 h after surgery; if < 150 mL, the patient will be randomized.

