### Randomization and intervention

Eligible patients will be randomized to either the heparin or tirofiban group in a 1:1 ratio utilizing an interactive online response system. Using the biased-coin minimization approach, a static randomization list will be created and applied taking three strata into consideration: research site, patient age group (< 70 and ≥ 70 years), and gender. Figure 1 depicts the enrollment and randomization procedures.

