## Assignment of interventions: allocation

### Sequence generation {16a}

All eligible subjects will be allocated by clinical staff to either heparin group or tirofiban group in a 1:1 ratio at 2 h after CE-CABG using an interactive web response system (IWRS). A static randomization list is generated and implemented within the system which accounted for three strata: study site, patient age group (< 70, ≥ 70 years) and gender group (male, female) using the biased-coin minimization method. Each center will have a designated user of the interactive system. This user will generate a random sequence for patients who meet criteria for enrollment and communicate the allocation to the research nurse.

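### Efficacy covariates are chosen by baseline significance tests, the named primary test cannot use them, and the minimisation factors enter no stated primary analysis

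*Protocol article*

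**What the plan says.** All analysis statements are in the protocol article, section Statistical methods for primary and secondary outcomes {20a}.

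- Baseline characteristics are tested between arms: "Patient characteristics will be compared using the two-sample" t-test or Wilcoxon test for continuous variables, chi-square or Fisher's exact test for categorical ones. No significance level for selection and no list of variables is given.
- The results decide the adjustment: "Variables that significantly differ between groups will be used as covariates for efficacy analysis".
- Primary efficacy: "The primary efficacy outcome will be evaluated using the chi-square test or Fisher’s exact test".
- Primary safety: "The primary safety outcome will be compared between groups using a one-sided non-inferiority test". No covariate is named.

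Allocation is described in Randomization and intervention and again in Sequence generation {16a}. Both balance on site, age group (below 70, 70 and over) and gender. Age and gender return only as subgroups, in the section on additional analyses {20b}.

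Under Standard procedure before randomization: "Chest tube blood loss will be evaluated 2 h after surgery; if < 150 mL, the patient will be randomized". Trial design {8} defines the safety endpoint as cumulative drainage over the first 24 h after surgery, so the volume measured before randomisation is part of it.

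**The concern.** Three things do not fit together.

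1. **Selection by p-value.** Under proper randomisation every baseline difference is a chance difference. A significance test of it does not show whether the variable predicts MACCE, which is what makes a covariate worth adjusting for. The rule fixes the adjusted model only after the data are seen, and different chance imbalances give different models.

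2. **Two efficacy analyses with no stated order.** The section promises covariates and then names a test that cannot use them. The Discussion calls the study positive at two-sided 0.05 without saying which analysis decides if the two disagree.

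3. **Balanced factors left out.** Minimisation removes between-arm variation due to site, age and gender. An unadjusted test still counts that variation in its standard error. If the factors are prognostic, the p-value is too large and some power is lost. The selection rule will not repair this, because balanced factors will almost never test as significant.

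**Working it through.** **Inputs from Sample size {14}.** Phase I: SD 500 mL, margin 200 mL, one-sided 2.5%, 90% power, 133 per group. Phase II: control rate 40%, two-sided 5%, 80% power, 730 recruited.

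**The plan's own figures.** Phase I: n = 2(1.96 + 1.2816)² × 500² / 200² = 131.3, so 132 per arm; the noncentral-t version gives 133, or 266 in total, as stated. Phase II: 40% against 30% needs 356 per arm, or 712 in total. The section's 712 is therefore reproduced as a total, with 25% read as a relative reduction. That wording is a separate matter; 40% against 30% is used here only to set power.

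**Step 1: spurious selection.** For k independent baseline variables tested at an assumed 5%, P(at least one significant by chance) = 1 − 0.95^k. The document does not give k.

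| k | 5 | 10 | 20 | 30 |
|---|---|---|---|---|
| P | 23% | 40% | 64% | 79% |

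**Step 2: does the rule recover precision?** Illustration: simple randomisation, 133 per arm, one covariate with correlation 0.5 to a continuous outcome, true difference 0.4 SD (200/500), 20,000 runs. Power is 90.3% unadjusted, 91.1% if the covariate is used only when significantly imbalanced, and 96.4% if it is pre-specified. The rule recovers almost none of the gain available.

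**Step 3: ignoring the balanced factors, binary outcome.** Three sites (Recruitment {15} names one hospital and two other centres) × two age groups × two genders give 12 strata. The simulation has 30 per arm per stratum (360 per arm), a mean control risk of 40%, exact balance within strata and 40,000 runs. It compares unadjusted chi-square with the stratified Cochran-Mantel-Haenszel (CMH) test. The power columns use a 25% relative reduction.

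| Assumed control risks across strata | Type I error, chi-square | Type I error, CMH | Power, chi-square | Power, CMH |
|---|---|---|---|---|
| all 40% | 5.0% | 5.0% | 80.4% | 80.4% |
| 30% and 50% | 4.8% | 5.0% | 80.9% | 82.0% |
| 20% to 50% | 4.5% | 5.0% | 80.7% | 82.2% |
| 15% to 65% | 4.0% | 5.1% | 81.4% | 84.2% |

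Monte Carlo standard error: √(0.05 × 0.95 / 40,000) = 0.11 points for type I error and √(0.8 × 0.2 / 40,000) = 0.2 points for power.

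Mechanism: chi-square uses a per-patient variance of 0.40 × 0.60 = 0.24. With strata at 30% and 50% the within-stratum variance is (0.21 + 0.25)/2 = 0.23, so the standard error is overstated by √(0.24/0.23) = 1.02. With 15% to 65% it is 0.211, a factor of 1.07. In large samples these factors give type I errors of 4.5% and 3.7%; the simulated values are slightly higher because counts are discrete.

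**Step 4: 0–2 h drainage as a phase I covariate.** SE = 500 × √(2/133) × √(1 − r²); power = Φ(200/SE − 1.96). With r = 0, SE = 61.3 mL, the half-width is 120 mL and power is 90.4%. The document does not give r. Because 2 h loss is limited to 0–150 mL, its SD is at most 75 mL (about 150/√12 = 43 mL if uniform). If it matters only as a component of the total, r is about 43/500 = 0.09 to 75/500 = 0.15. Power is then at most 91.0% and the half-width still about 119 mL.

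**The case against.** **The two analyses can be read benignly.** Chi-square may be primary and the covariate model supplementary. On that reading the primary test does not depend on the data, and selection affects only a secondary result. This is fair, but the text does not state that order, and a supplementary model chosen by baseline tests is still badly specified.

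**The loss is modest.** This stands. With strata at 30% and 50% the type I error is 4.8% and the loss about 1 point of power; the larger figures need stronger assumed prognostic effects.

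Three stronger readings are tempting and are not supported:

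- *That the trial risks excess false positives.* The departures found are conservative. The only figures above 5%, such as 5.1% for the stratified test, are within about one Monte Carlo standard error of it.
- *That omitting 2 h drainage is an error with a large cost.* Correlations of 0.3 to 0.5 would give 92.8% to 96.5% power, but they require early loss to predict later bleeding, which the document does not show. The unadjusted non-inferiority test is valid and meets its planned power. The article does not say that test is unadjusted, and its covariates may be in a document not shown.
- *That the allocation wording shows which method is wrong.* The article says "Using the biased-coin minimization approach, a static randomization list will be created and applied". Minimisation depends on patients already enrolled, so a fixed list cannot implement it as usually understood. This is a separate inconsistency. Recruitment began in September 2022, and the article alone does not show which method is running.

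**Conclusion.** The point holds for the efficacy analysis. The selection rule is stated outright, so it is not a detail left to an analysis plan. It selects by chance, and its place beside a test without covariates is undefined. Both conclusions follow from the text alone.

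The sizes rest on assumptions. The 23% to 79% range assumes a 5% selection level, independent variables and k from 5 to 30. The conservatism (type I error about 4.0% to 4.8%) and the loss of roughly 1 to 3 points of power assume that the minimisation factors are prognostic to the degree tabulated, that balance within strata is exact (minimisation balances margins only approximately), and that 40% against 30% is the intended effect. If the factors are not prognostic, neither loss arises.

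This should be changed because it makes the deciding analysis unambiguous at no cost, not because the planned test would mislead. For phase I, adjustment is an optional refinement whose gain is unknown and may be under 1 point of power.

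**What to change.** 1. Delete the sentence that makes significantly different variables into covariates. Baseline characteristics can be described without tests.
2. Name one primary efficacy analysis adjusted for site, age group and gender: for example a Mantel-Haenszel test, or logistic regression with a standardised risk difference. State that it alone decides the two-sided 0.05 claim. Keep chi-square or Fisher's exact test as a sensitivity analysis.
3. Optionally, pre-specify 0–2 h drainage and the three minimisation factors as covariates in a linear regression of 24 h drainage, comparing the upper confidence limit with 200 mL.
4. Separately, reconcile the static-list and minimisation wording in Randomization and intervention and in Sequence generation {16a} with the method actually in use.

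**Cost:** wording only. The minimisation factors are needed to allocate each patient and 2 h drainage is measured before randomisation, so no new data or patients are required. As recruitment has started, make the change by dated amendment before those deciding it see comparative results.
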